#### Data analysis

Baseline data consisting of demographic data (e.g., age, sex, diabetes, smoking status), medical history and the Kellgren–Lawrence grading will be summarised by operation type and overall and baseline imbalances will be explored.

The analysis of Oxford Hip Score and visual analogue scale will adopt the intention-to-treat approach, analysing all patients according to their randomly assigned operation type. The primary parameter Oxford Hip Score assesses 12 items on symptoms and functional status; the sum of the scores for the 12 items yields an overall score with range 0 to 48, where higher overall Oxford Hip Scores represent better outcomes.

The change from pre-operation to post-procedure in overall Oxford Hip Score will be analysed using a mixed-model repeated measures analysis, including as fixed in the model the categorical effects operation type, visit and operation type by visit interaction, and the stratification factor Kellgren–Lawrence grade, as well as the fixed continuous covariates pre-operation overall Oxford Hip Score and pre-operation overall Oxford Hip Score by visit interaction.To account for repeated measurements within a patient, an unstructured (co)variance structure will be used to model within-patient errors, whereby a patient is nested by surgeon.To account for potential clustering of the outcome due to a single surgeon using only one operation type, robust standard errors will be used. This primary model will include all patients with a pre-operation and at least one post-procedure overall Oxford Hip Score.

The primary hypothesis will be examined by three contrasts evaluating the change from pre-operation to 24 months post-procedure in overall Oxford Hip Score for the posterior versus Hardinge approach, the posterior versus anterior approach, and the Hardinge versus anterior approach using an alpha level of 1.67% for each contrast to allow for the three comparisons. The primary hypothesis will be rejected if at least one of the three comparisons reaches statistical significance using the two-sided Holm–Bonferroni-adjusted alpha level. An estimate and corresponding two-sided multiplicity-adjusted 98.33% confidence interval will be provided for each comparison. This analysis method uses a model-based approach to handle missing data providing valid inference if the missing data mechanism is ignorable (i.e., missing completely at random or missing at random). A range of sensitivity analyses to examine the robustness of the primary model results will be performed to explore the impact of the results of different missing data techniques under the same and under different missingness assumptions.

The primary model will be extended to include potential confounders, such as age, sex, diabetes or smoking status, to obtain adjusted treatment effect estimates. To investigate whether there is a different treatment effect between the subgroups defined by the Kellgren–Lawrence grade, appropriate interaction tests will be performed. The key secondary parameter measuring self-reported pain will be measured using a visual analogue scale with range 0 to 100%, where lower values represent a better outcome, and will be analysed similarly to the primary parameter.

Complications will be reported for all randomised patients who had their surgery according to the operation type they actually received. The number and percentage of patients with dislocation, infection, intraoperative and periprosthetic fractures during the entire post-procedure trial period will be reported by operation type and operation types will be compared using a modified Poisson model within the model operation type and the subgroups defined by the Kellgren–Lawrence grade whilst accounting for clustering by surgeon via robust standard errors. Residual regional pain measured using a visual analogue scale will be investigated similarly to the key secondary parameter. A two-sided alpha level of 5% will be used throughout, except for the primary parameter.

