#### Randomisation and enrolment

The randomisation list will be computer-generated by an independent statistician. A stratified block permuted randomisation will be used with the Kellgren–Lawrence grading scale (grade 0–2 vs. grade 3–4) as the stratification variable [24]. The block size will not be disclosed, to ensure concealment. Randomisation will be enabled through a secure, web-based application.

The surgeons performing the operation will be assigned to an operation type according to their expertise. Each surgeon will perform a single operation type and each operation type will be conducted by three surgeons.

A patient will be managed by one of the three surgeons corresponding to the treatment group the patient is randomly assigned to. It is anticipated that each surgeon will treat roughly the same number of patients.

The study will enrol a total of 243 patients to be treated by nine orthopaedic surgeons at Western Health; this accounts for approximately 81 patients per operation type.

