#### Sample size

Sample size is computed on the basis of our primary hypothesis that at least one of the three surgical methods will be superior to one other surgical method for total hip replacement, as measured by the change from pre-operation to 24 months post-procedure in the overall Oxford Hip Score. The minimal clinically important difference is at least five points and the best estimate for the standard deviation is nine points [25–28]. To control for the Type I error rate due to three treatment comparisons, a Holm–Bonferroni multiplicity adjustment will be used (i.e., a two-sided significance level of 0.0167 instead of 0.05). Using a two-sample *t* test, this leads to a sample size of 70 patients per operation type to obtain 80% power. This sample size needs to be increased because of two factors. Each surgeon will only perform one surgical method and as a result each patient cannot be assumed to generate independent observations because patients are clustered by surgeon. As a result, the sample size is inflated by 2.2% (i.e., a factor [1 + (*m* − 1) × intracluster correlation coefficient]) to achieve the variance that would have been anticipated had there been no clustering, assuming that each surgeon will treat 23 (*m* = 23) patients and the intracluster correlation coefficient is 0.001 [29, 30]. In addition, a drop-out rate of 10%, which includes a mortality of 2%, is anticipated at 24 months post-procedure [31], leading to an additional 11.1% increase in sample size.

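### Robust standard errors on nine surgeons, three per arm, do not hold the 1.67% level per contrast unless corrected for few clusters, and a valid test has well under 80% power

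*Protocol article*

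**What the plan says.** Under Randomisation and enrolment, surgeons are nested in arms: "Each surgeon will perform a single operation type and each operation type will be conducted by three surgeons". That makes nine surgeons in all, with roughly equal loads expected.

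Under Data analysis, the primary mixed model for repeated measures has fixed effects for operation type, visit and covariates, and an unstructured within-patient covariance. On surgeons it states: "To account for potential clustering of the outcome due to a single surgeon using only one operation type, robust standard errors will be used". The three pairwise contrasts at 24 months are tested "using an alpha level of 1.67% for each contrast to allow for the three comparisons", and "An estimate and corresponding two-sided multiplicity-adjusted 98.33% confidence interval will be provided for each comparison". The modified Poisson model for complications relies on the same device, there explicitly for clustering by surgeon.

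Under Sample size, the level is "a two-sided significance level of 0.0167 instead of 0.05", chosen to control Type I error over three comparisons. Clustering enters only as a design effect of 1.022, from 23 patients per surgeon and an intracluster correlation (ICC) of 0.001.

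**The concern.** A sandwich variance estimates between-cluster variability from the clusters themselves and is justified when there are many. Here each contrast compares three surgeons with three others. Two things go wrong in the plain form: the variance estimate is too small on average, and it is very noisy, while the test treats it as nearly known. Both make the statistic too large under the null.

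The effect does not shrink with a small ICC, because it comes from the number of clusters and not from how alike patients of one surgeon are. Assuming 0.001 is therefore no protection. At stake are the Type I error rate that the multiplicity adjustment is meant to control, the coverage of the 98.33% intervals, and the risk of declaring an approach superior because of chance differences among nine surgeons.

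**Working it through.** **Inputs from the protocol.** Level 0.05/3 = 0.0167; difference 5 points, SD 9 ("The minimal clinically important difference is at least five points and the best estimate for the standard deviation is nine points"); 3 surgeons per arm, 9 in total; 81 patients per arm; 10% drop-out; ICC 0.001. Evaluable patients: 243 × 0.9 / 9 = 24.3 per surgeon, taken as 24, or 72 per arm. ICCs of 0.01 and 0.05 and unequal loads of 10/20/40 are assumptions, used to show the range.

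**The plan's own figure.** A two-sample t test at 0.0167 has 79.8% power with 69 per arm and 80.5% with 70. This agrees with the protocol: "this leads to a sample size of 70 patients per operation type to obtain 80% power". Then 70 × 1.022 / 0.9 = 79.5, so 80 per arm; the stated 81 is 3 × 27. The arithmetic is sound, but it treats the variance as if it came from many independent units.

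**Type I error, clustering by surgeon.** With J = 3 equal clusters per arm:
- The plain sandwich variance of a contrast has expectation (J − 1)/J = 2/3 of the truth.
- It rests on 2 × (J − 1) = 4 df.
- Under the null the statistic is therefore distributed as √1.5 × t(4), whatever the ICC, and the error is P(|t(4)| > c/√1.5) for critical value c.

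For the plain sandwich with a normal reference, c = 2.394 and 2.394/1.225 = 1.955, so P(|t(4)| > 1.955) = 12.2%. If the variance is multiplied by 9/8, √1.5 becomes √(1.5 × 8/9) = 1.155. If it is unbiased, the factor is 1.

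| Reference | c | Plain | 9/8 correction | Unbiased |
|---|---|---|---|---|
| Normal | 2.394 | 12.2% | 10.7% | 7.5% |
| t, 8 df | 3.016 | 7.0% | 5.9% | 3.9% |
| t, 6 df | 3.287 | 5.5% | 4.7% | 3.0% |
| t, 4 df | 3.961 | 3.2% | 2.7% | 1.67% |

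A t reference with 200 df gives 12.0% for the plain form. Coverage in the plain, normal-reference case is 100 − 12.2 = 87.8%.

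**Simulation (no true difference).**
- Plain, normal reference: 12.2-12.3% per contrast and 27% for any of three, for ICC 0 to 0.05.
- Same, adding baseline score and Kellgren-Lawrence grade as covariates, complete data: 12.0-12.3%.
- 9/8 correction with t on 8 df: 5.9-6.0% per contrast, 14-15% for any of three.
- Unbiased variance with 4 df: 1.6-1.7% and 4.4-4.5%.
- Loads 10/20/40, plain, normal reference: 15-16%. The equal-load correction with 4 df then gives 2.4-2.6%.

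**Type I error, sandwich at patient level.** Surgeon clustering is ignored, so the error is P(|Z| > 2.394/√(1 + 23 × ICC)):
- ICC 0.001: √1.023, 1.8%
- ICC 0.01: √1.23, 3.1%
- ICC 0.05: √2.15, 10.3%

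Simulation agrees: 1.9-2.1%, 3.2-3.4% (up to 3.7% with loads 10/20/40) and 10.3%.

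**Power of a valid test.** At ICC 0.001 the standard error of a contrast is √(2 × 81 × 1.023 / 72) = 1.517, so the noncentrality is 5/1.517 = 3.30.
- Against t(4), c = 3.961: 41%.
- Against t(6), c = 3.287: 55%.
- Random surgeon effect by REML, simulated with 6 df (or N − 3 when the surgeon variance is estimated as zero): about 58%.

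At an assumed ICC of 0.01 these become 35%, 46% and 49-50%. The REML analysis had a Type I error of 0.9-2.0% per contrast.

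**The case against.** The strongest reply is that the article fixes neither the sandwich variant nor the reference distribution. Such details commonly sit in an analysis plan, which is not shown. A CR2 variance with Satterthwaite df is itself a robust standard error, so the wording does not exclude a valid analysis. That stands, and it rules out a reading that a reader might be tempted to make: that the trial's true error per contrast is 12%, that its intervals cover 88%, and that the multiplicity adjustment is therefore void. Those statements need surgeon-level clustering, no bias correction and a near-normal reference together. The document states only the purpose, which points to surgeon level.

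It can also be said that a patient-level sandwich gives about 1.8% at the protocol's ICC, which is close to nominal. True, but it then provides no allowance for surgeon clustering, against the sentence's stated purpose, and it depends wholly on the ICC really being that small.

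Finally, the random-effect remedy is not exact: it is conservative near ICC 0.001 and slightly liberal at 0.05, so preferring it to a corrected sandwich is partly a matter of taste.

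What the reply does not remove is that the protocol commits the primary test to a named class of estimator. The usual forms of that class miss the stated level with this number of surgeons, and only a specific, non-default correction restores it.

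**Conclusion.** The point holds in conditional form. With three surgeons per arm, a surgeon-clustered sandwich has an error of up to about 12% per contrast and 27% familywise (plain, normal or large-df reference). With t on 8 df the error is about 6-7%. Among the sandwich versions computed, only an unbiased variance with 4 df gives 1.67%. At patient level the error runs from about 1.8% at ICC 0.001 to about 10% at an assumed 0.05. The flat 12% is the upper end for equal surgeon loads and not a property that the documents establish.

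The planned 80% power is not available to a valid surgeon-level analysis: it is about 41-58% at ICC 0.001.

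These figures assume nine surgeons with near-equal loads, each in one arm, and complete 24-month data. The illustrative list under Intervention puts one surgeon under two approaches and names only eight. It conflicts with the single-approach rule and the count of nine, and the two should be reconciled because they define the clusters.

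**What to change.** In Data analysis, replace the unqualified reference to robust standard errors in the primary model with a method valid for few clusters. There are two options:
- a random surgeon effect nested in operation type, fitted by REML with Kenward-Roger degrees of freedom;
- a surgeon-clustered CR2 variance with Satterthwaite degrees of freedom.

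State that the cluster is the surgeon, and derive the 98.33% intervals from the same degrees of freedom. A t test on the nine baseline-adjusted surgeon means (6 df) is a useful check; it gave 1.6-1.7% error in simulation. The complications model should receive the same scrutiny, since it uses the same device.

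The wording change is small, but its consequence is not. Intervals widen, and power for 5 points falls from 80% to about 41% (4 df), 55% (6 df) or 58% (REML surgeon effect) at ICC 0.001, and lower if the ICC is larger. The Sample size section should restate power for the chosen method. The binding limit is the number of surgeons, so an analysis change alone cannot recover the planned power.

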#### Primary outcome

The primary outcome measure for this study is the Oxford Hip Score; this will be recorded as shown in Fig. 1 at the following time points: pre-operatively and post-operatively at 6 weeks, 6, 12 and 24 months. The primary outcome measure for which our study is powered is the Oxford Hip Score at 24 months.

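### The primary model leaves out randomised patients who have a 24-month Oxford Hip Score but no pre-operation score; the set is narrower than the intention-to-treat wording, and the loss is avoidable

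*Protocol article*

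**What the plan says.** The protocol article's Data analysis section says that the Oxford Hip Score and pain analyses "will adopt the intention-to-treat approach, analysing all patients according to their randomly assigned operation type". Two sentences then fix the primary model. The response is change: "The change from pre-operation to post-procedure in overall Oxford Hip Score will be analysed using a mixed-model repeated measures analysis". The covariates include the "fixed continuous covariates pre-operation overall Oxford Hip Score and pre-operation overall Oxford Hip Score by visit interaction".

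The section next sets the condition for entry: "This primary model will include all patients with a pre-operation and at least one post-procedure overall Oxford Hip Score". It describes the missing-data approach as "providing valid inference if the missing data mechanism is ignorable (i.e., missing completely at random or missing at random") and promises sensitivity analyses with other missing-data techniques, which it does not specify.

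The Primary outcome section names the endpoint as a score, not a change: "The primary outcome measure for which our study is powered is the Oxford Hip Score at 24 months". The Sample size section and the three primary contrasts refer to the change from pre-operation to 24 months. The only loss allowance is in the Sample size section: "a drop-out rate of 10%, which includes a mortality of 2%, is anticipated at 24 months post-procedure". The visual analogue scale for pain is to be analysed in the same way as the primary parameter.

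**The concern.** The entry rule has two conditions. Requiring at least one post-procedure score is unavoidable, short of imputing whole outcome profiles. Requiring a pre-operation score is different, because in this model that score serves mainly as a covariate. A patient who was randomised, operated on and followed to 24 months would leave the primary analysis because one baseline form is missing, although the outcome named in the Primary outcome section was observed.

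Three things are at stake. The analysed set is smaller than a reader of the intention-to-treat sentence would expect. The three contrasts lose precision that the trial has already paid for. And the statement about ignorable missingness does not reach these patients, because they are removed before the model is fitted. The pain analysis would inherit the same rule.

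**Working it through.** **1. Is the baseline needed to estimate the contrast?** Let Y be the score at 24 months, B the pre-operation score and A the arm. Leaving out Kellgren–Lawrence grade for brevity, the planned model at that visit is

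Y − B = a + d·A + b·B + error.

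Adding B to both sides gives

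Y = a + d·A + (b + 1)·B + error.

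The arm effect d is the same in both; only the coefficient of B moves, by 1. The baseline-by-visit interaction lets this hold at each visit separately. A patient with Y but no B therefore carries information on d.

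**2. The plan's sample size.** Inputs from the Sample size section: difference 5, SD 9, two-sided alpha 0.0167, power 80%, design factor 1 + (23 − 1) × 0.001 = 1.022, drop-out 10%. A two-sample t test (noncentral t) needs 69.3, so 70 per arm, with power 80.5% at 70. Inflated, 70 × 1.022 / 0.9 = 79.5, against the stated 81. The plan's figure is reproduced within rounding.

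**3. Slack.** Needed after clustering: 70 × 1.022 = 71.5 evaluable patients per arm. Expected: 81 × 0.9 = 72.9. The slack is 1.4 patients per arm, or 1.9%. The 10% is for drop-out by 24 months and makes no separate provision for missing baselines.

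**4. Power if patients without a baseline are excluded.** The missing rate p is not in the document, so p = 0 to 10% is an assumption. Effective n per arm = 81 × 0.9 × (1 − p) / 1.022. The unadjusted column follows the plan (SD 9). The adjusted column uses SD 9 × √(1 − r²), with an assumed pre/post correlation r of 0.2 to 0.4 and 9 read as the unadjusted SD.

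| p | patients of 243 | effective n per arm | unadjusted power | power, r = 0.2 to 0.4 |
|---|---|---|---|---|
| 0 | 0 | 71.3 | 81.3% | 83.1 to 88.3% |
| 2% | about 5 | 69.9 | 80.4% | 82.2 to 87.6% |
| 5% | about 12 | 67.8 | 79.0% | 80.8 to 86.4% |
| 10% | about 24 | 64.2 | 76.4% | 78.3 to 84.2% |

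Unadjusted power crosses 80% at just under 3% missing. With r = 0.2 the crossing is at about 6.7%.

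**5. Variance cost of exclusion compared with keeping the patients.** With unit variance, the variance per arm is proportional to (1 − r²) / (1 − p) under exclusion, and to (1 − p)(1 − r²) + p if the missing covariate is filled with the all-arm mean. The ratio of the two is

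(1 − r²) / {(1 − p) × [(1 − p)(1 − r²) + p]}.

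For p = 0.05 and r = 0.2: 0.96 / (0.95 × 0.962) = 1.050. For p = 0.05 and r = 0.4: 0.84 / (0.95 × 0.848) = 1.043. The same formula gives 1.017 to 1.020 at 2% missing and 1.090 to 1.107 at 10%. A simulation of the 24-month comparison (73 per arm, 20,000 runs, baselines missing at random) gave 1.014 to 1.020, 1.043 to 1.049 and 1.096 to 1.111. The rounded increases are 2%, 5% and 10%. The ceiling is 1 / (1 − p), for example 5.3% at 5% missing.

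**The case against.** A reader might infer that the rule contradicts the intention-to-treat commitment. The documents do not support that. The commitment is to "analysing all patients according to their randomly assigned operation type", which settles the arm a patient is counted in, and the model keeps to it; complications, by contrast, are compared by the operation received. Requiring a baseline and one follow-up score is a common modified intention-to-treat set, and it is disclosed in the same section. The set proposed below also omits some randomised patients, namely those with no post-procedure score.

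It can also be said that the tested endpoint is change, which does not exist without a baseline. That is true of the response as written. It does not make the exclusion necessary, because the contrast can be estimated from the score itself (step 1).

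A reader might further infer that the trial becomes underpowered. That is not shown. No missing rate is given, and it is probably low: clinic attendance before surgery is mandatory, patients unable to complete the scores are excluded, and the clinic collects these measures routinely. The unadjusted power figures ignore the baseline adjustment in the plan and count every drop-out as contributing nothing, although the repeated-measures model uses earlier visits. Bias is not shown either: patients and the research team are blinded before surgery, so a missing baseline should be largely unrelated to arm. The article does not say, however, whether the score is taken before randomisation.

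Finally, the planned sensitivity analyses might bring these patients back. The text does not say so, and they would not change the primary result. Details of baseline imputation may properly sit in an analysis plan that is not shown, but the entry rule itself is fixed here.

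**Conclusion.** The point holds as an avoidable loss of precision and a label that is wider than the analysed set. It is not an error that invalidates the analysis. Its size depends on an unknown missing-baseline rate: the variance of a contrast rises by about 2%, 5% and 10% at 2%, 5% and 10% missing, on the assumption that baselines are missing independently of arm and that the pre/post correlation is 0.2 to 0.4. On the plan's unadjusted calculation, power dips below 80% from about 3% missing. Under the assumed correlation it remains above 80% at 5% missing, and at 10% it falls short only towards the low end of the correlation range. If almost all baselines are recorded, the effect is negligible.

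**What to change.** Replace the entry sentence with a rule that the primary model includes every randomised patient with at least one post-procedure Oxford Hip Score, analysed by assigned arm. State one way of keeping patients whose pre-operation score is missing:

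- a constrained longitudinal model, with the pre-operation score in the response vector and a baseline mean common to the three arms; or
- the visit score as the response, with a missing baseline covariate filled by the mean over all arms within Kellgren–Lawrence stratum.

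Both rest on the baseline being unaffected by the allocation. Apply the same rule to the pain scale. The three 24-month contrasts, the alpha level and the confidence intervals stay as they are. If the present rule is kept instead, the set should at least be called modified intention-to-treat.

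The cost is one sentence in the protocol or analysis plan and a few lines of code, with no new data and no additional patients. It should be settled before outcomes are compared by arm.

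### The primary multiplicity method is called Holm–Bonferroni but is fixed at 1.67% for every contrast, which is plain Bonferroni; the two can differ on which pairs of approaches are declared different

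*Protocol article*

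**What the plan says.** In the Protocol article, the Sample size section states that "a Holm–Bonferroni multiplicity adjustment will be used (i.e., a two-sided significance level of 0.0167 instead of 0.05". It then sizes the trial with a two-sample t test at that level: "The minimal clinically important difference is at least five points and the best estimate for the standard deviation is nine points", and "this leads to a sample size of 70 patients per operation type to obtain 80% power".

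The Data analysis section sets up three contrasts at 24 months (posterior versus Hardinge, posterior versus anterior, Hardinge versus anterior), "using an alpha level of 1.67% for each contrast to allow for the three comparisons". The decision rule follows: "The primary hypothesis will be rejected if at least one of the three comparisons reaches statistical significance using the two-sided Holm–Bonferroni-adjusted alpha level". For estimation, a "two-sided multiplicity-adjusted 98.33% confidence interval will be provided for each comparison".

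For the primary parameter no ordering of p values, no stopping rule, and no threshold of 0.025 or 0.05 appears.

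**The concern.** Holm's procedure has no single adjusted level. With three tests it is a sequence: the smallest p value is compared with 0.05/3, the next with 0.05/2 and the last with 0.05, and testing stops at the first failure. The protocol gives the method this name and then defines it as one fixed level for all three contrasts, which is Bonferroni. Name and number cannot both be followed beyond the first step.

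The contradiction concerns the primary endpoint, and the protocol itself fixes both sides of it, so it is not a detail left to a later document. An analysis plan that follows the name departs from the 1.67%; one that follows the 1.67% departs from the name. If the choice is made after the p values are known, the analyst in effect chooses which pairs of approaches are declared different, in a trial meant to compare the three directly.

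There is also a slip in the decision sentence. The Sample size section defines the primary hypothesis as superiority of at least one method over another, while the Data analysis section says that the primary hypothesis is rejected when a contrast is significant. What is rejected is the null hypothesis, which is set out under Statistical considerations.

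**Working it through.** **Inputs from the protocol.** Difference 5 points, SD 9, two-sample t test, 70 per arm for 80% power, two-sided 0.0167, cluster inflation 2.2% and drop-out 10% (Sample size); about 81 per arm and 243 in total (Randomisation and enrolment). **Assumed:** how the three arm means are spaced, which the protocol does not give.

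**1. The plan's own figures.**
- 0.05/3 = 0.0167 and 1 − 0.05/3 = 98.33%, so level and interval agree with each other and both are Bonferroni.
- Noncentral t, difference 5, SD 9, α = 0.0167: the smallest n with at least 80% power is 70 per arm (power 80.5%). The stated 70 is reproduced.
- 70 × 1.022 / 0.9 = 79.5, so 80 per arm, close to the stated 81.

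**2. The two rules side by side.**

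| Ordered p value | As written | Holm | Rules disagree when p lies in |
|---|---|---|---|
| Smallest | 0.0167 | 0.05/3 = 0.0167 | never |
| Second | 0.0167 | 0.05/2 = 0.025, if the first is rejected | 0.0167 to 0.025 |
| Third | 0.0167 | 0.05, if the second is rejected | 0.0167 to 0.05 |

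**3. Marginal power at each threshold** for a 5-point difference with 70 per arm (t test): 80.5% at 0.0167, 84.5% at 0.025, 90.4% at 0.05.

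**4. Simulation of the full procedures.** Evaluable patients per arm: 81 × 0.9 = 72.9. Allowing for the stated design effect, 72.9/1.022 = 71.3, so the standard error of an arm mean is 9/√71.3 = 1.066 and that of a contrast is 1.066 × √2 = 1.507. Normal test.

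| Assumed arm means | Quantity | Fixed 1.67% | Holm |
|---|---|---|---|
| 5, 0, 0 | power per true contrast | 82% | 85% |
| 5, 0, 0 | both true differences found | 72% | 77% |
| 5, 2.5, 0 | power for each 2.5-point contrast | 23% | 29% |
| 10, 5, 0 | all three differences found | 65% | 82% |

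The two rules reach a different decision on at least one contrast in about 7%, 12% and 18% of simulated trials in the configurations 5, 0, 0; 5, 2.5, 0; and 10, 5, 0 respectively.

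**5. What does not move.** The probability of at least one rejection is identical under both rules: 92.7% for 5, 0, 0 and 84.1% for 5, 2.5, 0. So is the error rate when all arms are equal, 4.4%. With exactly one true null, the family-wise error of the fixed rule is 1.7%. Holm's stays within 5.0%.

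**6. An optional sharper rule.** With three pairwise contrasts, if one pair differs, at most one of the other two nulls can be true. After a first rejection at 0.0167, both remaining contrasts can therefore be tested at 0.05 (Shaffer). For 5, 0, 0 this gives 88% per true contrast and 84% for both, with a largest simulated family-wise error of 5.0%. This method is not in the plan and does not measure the contradiction.

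**The case against.** The strongest reply is that the rule as written is valid. A fixed 1.67% with 98.33% intervals is coherent Bonferroni: it controls the family-wise error, its tests agree with its intervals, and it errs on the conservative side. The primary claim needs only that "at least one of the three comparisons reaches statistical significance using the two-sided Holm–Bonferroni-adjusted alpha level", and Holm's first step is the same 0.0167. Sizing on 0.0167 is the usual way to plan a Holm procedure. The fixed level already gives 80.5% for any single 5-point contrast with 70 per arm, so the planned power is met. All of this stands, and it limits the weight of the point.

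A reader might infer more than the documents support, in three ways.
- That the trial is underpowered or its type I error inflated. Neither follows: the power given up is a gain that the named method would have brought on later contrasts, and the fixed level is stricter than Holm.
- That any second p value up to 0.05 is in dispute. It is not: between 0.025 and 0.05 a second ordered p value fails under both readings. It would pass only under Shaffer's rule, which the protocol never mentions.
- That the slip about rejecting the primary hypothesis could reverse the conclusion. The null is stated explicitly elsewhere, so that is a wording error only.

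The reply does not remove the contradiction. The protocol undertakes to report all three contrasts separately, and for the second and third it gives a name and a number that can disagree.

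**Conclusion.** The point holds as a contradiction in the specification of the primary analysis. Its reach is limited to which pairs are declared different after the first rejection. Between the protocol's two readings the cost is about 3 percentage points of power per true contrast and 5 points for finding both (82% to 85%, 72% to 77%) when one arm is better by 5. It is larger when all three arms differ by 5-point steps (65% to 82% for finding all three). These figures rest on the protocol's SD of 9, its intracluster correlation and drop-out rate, and on assumed spacings of the arm means; the thresholds and the disputed ranges of p need no such assumption. It is worth correcting before outcome data by arm are seen, because the correction is cheap and removes a choice that could otherwise be made with the p values in hand.

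**What to change.** - **Data analysis:** replace the fixed 1.67% per contrast with Holm's rule. Order the three p values, compare them with 0.0167, 0.025 and 0.05 in turn, and stop at the first that is not rejected. Shaffer's thresholds 0.0167, 0.05 and 0.05 are a valid option for three pairwise contrasts if the authors want the extra power.
- **Sample size:** say that 0.0167 is the first-step level, used for sizing. No number there changes.
- **Intervals:** keep the 98.33% intervals and label them Bonferroni simultaneous intervals.
- **Decision sentence:** write that the null hypothesis is rejected, not the primary hypothesis.

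The cost is wording only, with no added patients. The one small downside is that a contrast rejected at a later step can have a 98.33% interval that includes zero, and the text should say so.
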